# Leveraging Community Health Workers and a Responsive Digital Health System to Improve Vaccination Coverage and Timeliness in Resource-Limited Settings: Protocol for a Cluster Randomized Type 1 Effectiveness-Implementation Hybrid Study

**DOI:** 10.2196/52523

**Published:** 2024-01-12

**Keywords:** childhood vaccinations, timeliness, vaccine hesitancy, digital health, community health workers, Tanzania, low- and middle-income countries, SMS, reminder, conditional incentive

## Abstract

**Background:**

Tanzania is 1 of 20 countries where the majority of unvaccinated and undervaccinated children reside. Prior research identified substantial rural-urban disparities in the coverage and timeliness of childhood vaccinations in Tanzania, with children in rural settings being more likely to receive delayed or no vaccinations. Further research is necessary to identify effective and scalable interventions that can bridge rural-urban gaps in childhood vaccination while accounting for multifaceted barriers to vaccination.

**Objective:**

This protocol describes a type 1 effectiveness-implementation hybrid study to evaluate Chanjo Kwa Wakati (*timely vaccination* in Kiswahili), a community-based digital health intervention to improve vaccination timeliness. The intervention combines human resources (community health workers), low-cost digital strategies (electronic communication, digital case management, and task automation), a vaccination knowledge intervention, and insights from behavioral economics (reminders and incentives) to promote timely childhood vaccinations.

**Methods:**

The study will be conducted in 2 predominantly rural regions in Tanzania with large numbers of unvaccinated or undervaccinated children: Shinyanga and Mwanza. Forty rural health facilities and their catchment areas (*clusters*) will be randomized to an early or delayed onset study arm. From each cluster, 3 cohorts of mother-child dyads (1 retrospective cohort and 2 prospective cohorts) will be enrolled in the study. The timeliness and coverage of all vaccinations recommended during the first year of life will be observed for 1200 children (n=600, 50% intervention group children and n=600, 50% nonintervention group children). The primary effectiveness outcome will be the timeliness of the third dose of the pentavalent vaccine (Penta3). Quantitative surveys, vaccination records, study logs, fidelity checklists, and qualitative interviews with mothers and key informants will inform the 5 constructs of the reach, effectiveness, adoption, implementation, and maintenance (RE-AIM) framework. The results will be used to develop an implementation blueprint to guide future adaptations and scale-up of Chanjo Kwa Wakati.

**Results:**

The study was funded in August 2022. Data collection is expected to last from February 2024 to July 2027.

**Conclusions:**

This study will address the lack of rigorous evidence on the effectiveness of community-based digital health interventions for promoting vaccination coverage and timeliness among children from sub-Saharan Africa and identify potential implementation strategies to facilitate the deployment of vaccination promotion interventions in low- and middle-income countries.

**Trial Registration:**

ClinicalTrials.gov NCT06024317; https://www.clinicaltrials.gov/study/NCT06024317

**International Registered Report Identifier (IRRID):**

PRR1-10.2196/52523

## Introduction

### Background

Globally, the number of children missing their first dose of the diphtheria-pertussis-tetanus (DPT) vaccine rose from 19 million in 2019 to 25 million in 2021 [1,2]. The vast majority (14.2 million, 78%) of such *zero-dose* children reside in 20 countries, including Tanzania [3]. As in other low- and middle-income countries (LMICs), substantial rural-urban disparities in routine childhood vaccination exist in Tanzania, with vaccination rates being lower in rural areas than in urban areas [4]. Using data from the 2015-2016 Tanzanian Demographic and Health Survey, we demonstrated gaps in vaccination coverage (receipt of each recommended vaccine dose by age 1 y) and timeliness (receipt of each vaccine dose within 28 d of the recommended age) for Tanzanian children [4]. The coverage of the first dose of the pentavalent vaccine (Penta1, which includes antigens of DPT, *Hemophilus influenzae*, and hepatitis B) was 79.4% nationally in this analysis, with the remaining 21% of children classified as zero dose [4]. We documented receipt of the third dose of the pentavalent vaccine (Penta3) in even fewer children (72.7%), suggesting dropouts in the multidose vaccine series. Finally, rural children had lower timeliness of vaccination (47.8% delayed for Penta3) than urban children (24.2% delayed for Penta3). New interventions are needed to reduce the number of children who are zero dose, receive delayed vaccines, or drop out and to close the rural-urban gap in vaccination [4,5]. Such interventions must consider multifaceted barriers to vaccination and variations in the availability of human resources and infrastructure in rural areas.

In prior research in southern Tanzania, we identified challenges with the availability of, and access to, vaccination services, including challenges with distance and transportation to health facilities, temporary nonavailability of vaccines owing to a lack of reliable refrigeration at health facilities, and vaccine wastage policies that prevented the use of multidose vials when clinics had low volumes of children to be vaccinated [6]. Service unreliability and lack of communication about service interruptions were noted as causes of frustration among mothers of vaccine-eligible children [6]. Our research also identified vaccine hesitancy owing to vaccine-related knowledge gaps and concerns. In general, rural mothers reported more vaccine-related knowledge gaps and concerns than urban mothers [6]. Despite challenges, vaccination intention was high among mothers, and conditional incentives were identified as a potential *nudge* to increase vaccination timeliness [7,8]. In addition, a community health worker (CHW)–delivered knowledge intervention was piloted and determined to be feasible to implement in rural areas. On the basis of the findings of this formative research and other published reports [9], we designed Chanjo Kwa Wakati (*timely vaccination* in Kiswahili, the most commonly spoken language in Tanzania), a community-based digital health intervention to improve childhood vaccination coverage and timeliness. The intervention seeks to combine human resources (CHWs), low-cost digital strategies (electronic communication, digital case management, and process automation), a vaccination knowledge intervention (counseling scripts addressing specific knowledge gaps), and insights from behavioral economics (reminders and incentives) to promote timely childhood vaccination.

### Objectives

This protocol describes our planned evaluation of the implementation and impact of Chanjo Kwa Wakati. The study seeks to contribute evidence to the literature in 3 key ways. First, although many studies have evaluated mobile phone–based reminders for promoting childhood vaccinations [10], evidence is lacking [9] for more complex community-based digital health interventions that target multifaceted barriers to vaccinations, such as those identified in our prior research [4,6,7]. Second, few community-based digital health interventions for promoting childhood vaccination have been evaluated using rigorous randomized controlled study designs, especially in sub-Saharan African countries and in rural areas [11-15]. Third, evidence on implementation strategies associated with deploying community-based digital health interventions in LMICs is limited but critically important for supporting scale-up in the context of highly resource-constrained national health systems. To bridge these gaps in the literature, we will use a type 1 effectiveness-implementation hybrid study [16,17] to evaluate the effectiveness of Chanjo Kwa Wakati in improving the timeliness of childhood vaccinations in rural areas in Tanzania and identify strategies that support its implementation. The detailed protocol of the study is presented in the following sections.

## Methods

### Study Overview and Aims

This type 1 effectiveness-implementation hybrid study [16,17] uses a cluster randomized trial to evaluate intervention effectiveness and mixed methods to describe implementation outcomes. A cluster randomized design was chosen because the delivery of the intervention is organized at the cluster level. In addition, there are ethical concerns with the randomization of intervention activities, including incentives, at the individual level in rural communities in Tanzania. The evaluation of the Chanjo Kwa Wakati intervention will be guided by the reach, effectiveness, adoption, implementation, and maintenance (RE-AIM) framework. The methods used in this study are described in accordance with the CONSORT (Consolidated Standards of Reporting Trials) checklist for cluster randomized studies (Multimedia Appendix 1). The study aims and hypotheses are described in the following subsections.

#### Aim 1

The first aim is to evaluate the effectiveness of Chanjo Kwa Wakati for increasing the timeliness of childhood vaccinations due by age 1 year compared with the standard of care. The effectiveness of Chanjo Kwa Wakati will be evaluated in a cluster randomized trial with 1200 mother-child dyads enrolled from the catchment areas of 40 rural health facilities (*clusters*) in 2 regions in Tanzania. Clusters will be randomized into an early or delayed onset study arm. The intervention will target the mother-child dyad; outcomes will be assessed at the child level. Our hypothesis is that Chanjo Kwa Wakati is effective for increasing the timeliness of childhood vaccinations due by age 1 year compared with the standard of care. The primary outcome measure used to evaluate intervention effectiveness will be a continuous measure of the timeliness of the third dose of the pentavalent vaccine (Penta3), due at age 14 weeks, and determined using the birth and vaccination dates abstracted from official vaccination cards issued for the child. A secondary outcome will be a binary measure of timeliness, defined as receipt of Penta3 within 28 days of the due date. Other outcomes measures include the timeliness and coverage of all other vaccine doses due by age 1 year.

#### Aim 2

The second aim is to evaluate the implementation factors associated with variation in intervention effectiveness and develop an implementation blueprint for intervention scale-up to other settings. Study logs, fidelity checklists, quantitative surveys, and qualitative interviews with mothers and key informants will be used to inform other constructs of the RE-AIM framework, specifically reach, adoption, implementation, and maintenance. Two key implementation outcomes of interest are participants’ reports of the receipt of intervention components (intervention fidelity) and their reports of intervention acceptability. Analyses of variation in intervention implementation at the cluster level and systematic variation in the effectiveness for aim 1 outcomes across children will guide the future optimization of Chanjo Kwa Wakati. The results will be used to develop an implementation blueprint to guide future adaptations and scale-up of Chanjo Kwa Wakati.

### Study Setting

The study will be conducted in 4 rural districts in Mwanza and Shinyanga regions in Tanzania. Both regions have large numbers of unvaccinated or undervaccinated children. The populations of Mwanza and Shinyanga region were estimated to be 3,699,872 and 2,241,299, respectively [18]. In 2022, only 56% of children aged 12 to 23 months in Mwanza region and 32.2% of children in Shinyanga region were estimated to have received all basic vaccinations, including one dose of Bacillus Calmette-Guerin vaccine, 3 doses of polio vaccine, 3 doses of DPT-containing vaccine, and one dose of measles-containing vaccine [19]. Fewer children aged 12-23 month were considered fully vaccinated according to the national vaccination schedule shown in Table 1 (32.8% in Mwanza and 2.5% in Shinyanga) [19]. Notably, 3.3% of children aged 12-23 months in Mwanza and 14.5% in Shinyanga were reported to have received no vaccinations. [19].

**Table 1 table1:** Routine childhood immunizations recommended in Tanzania before age 1 year.

Antigen	Age at vax due date
Bacillus Calmette-Guerin (BCG) and oral polio vaccine (OPV) 0	At birth or first contact
OPV1; pentavalent vaccine comprising antigens of diphtheria, pertussis, tetanus, *Hemophilus influenza* B, and hepatitis B (Penta) 1; pneumococcal vaccine (PCV) 1; and rotavirus vaccine (Rota) 1	6 weeks
OPV2, Penta2, PCV2, and Rota2	10 weeks
OPV3, Penta3, PCV3, and injectable polio vaccine (IPV)	14 weeks
Measles and rubella 1	9 months

### Intervention Components

Chanjo Kwa Wakati focuses on individual-level barriers to timely vaccination to complement the Tanzanian government’s efforts to strengthen vaccination systems and reduce structural barriers [20]. Chanjo Kwa Wakati comprises the following individual-level intervention components: a vaccination knowledge intervention, reminders about upcoming vaccination due dates, service notifications, and conditional incentives for timely vaccination (Table 2). The intervention’s target population is the mother-child dyad from the time of pregnancy (third trimester) until the child is aged 1 year. Intervention activities are targeted toward the mother, whereas the timeliness of Penta3 (primary outcome) and other vaccinations recommended before age 1 year (secondary outcomes; Table 1) is assessed for the child.

**Table 2 table2:** The Chanjo Kwa Wakati intervention.

Timing	Activities	Detailed description of activities
Last trimester of pregnancy	Enrollment Registration in digital health system Knowledge intervention Baseline assessment^a^	Informed consent^a^ Register pregnancy and phone numbers in the digital health system Identify knowledge gaps for an individualized knowledge intervention based on a study by Vasudevan et al [6] Assess postintervention change in vaccination knowledge and attitudes as well as potential correlates of coverage and timeliness^a^
≤4 wk after the date of delivery	CHW^b^ phone call or home visit	Ascertain date and place of birth as well as the receipt of vaccinations due at birth Register the birth, record the 6-wk vaccination due date, and update phone numbers in the digital health system
Before each vaccination due date (6, 10, and 14 wk, and 9 mo)	SMS text message reminders with incentive offers Backup: CHW phone calls or home visits Knowledge intervention	Messages are sent to the mother and vaccine advocates 7 d and 1 d before each vaccination Messages are individualized and account for information on service interruptions Messages include conditional incentive offers Individualized knowledge intervention focused on vaccinations due at an upcoming visit
≤1 wk after each vaccination due date	CHW phone call or home visit	Verify vaccination status and date against vaccination card and issue incentive as appropriate Update vaccination due dates (and thus reminders) as necessary
12-15 mo after birth	Follow-up assessment^a^	Validate vaccination coverage and dates using vaccination cards^a^ Issue incentive as appropriate

^a^Research activity. All other activities are intervention activities.

^b^CHW: community health worker.

#### Individualized Knowledge Intervention

The knowledge intervention consists of 9 true or false statements that assess key knowledge gaps about childhood vaccinations. A brief counseling script is provided with each statement that will be read out by the CHW after an incorrect response. Statements are based on prior research in Tanzania [6]. Statements and counseling scripts were tested extensively for content, comprehension, and cultural appropriateness with national key informants from Tanzania’s Immunization and Vaccines Development program, regional and district health officials, CHWs, and pregnant women from rural Tanzania. In addition to the in-person individualized vaccination education provided by CHWs, SMS text message–based vaccination promotion messages, sent via the Chanjo Kwa Wakati digital health system, will be individualized to each participant’s knowledge gaps and aligned with the child’s vaccination schedule.

#### Vaccination Reminder Messages

CHWs will verify the due date for the next vaccination using the child’s vaccination card and update the child’s information in the Chanjo Kwa Wakati digital health system. The system will automatically schedule SMS text message reminders to be sent 7 days and 1 day before each vaccination due date. The SMS text messages will include the name of the intended recipient, the child’s name, the vaccination due date, and other relevant information.

#### Service Notifications

In the event of stockouts or service nonavailability, SMS text messages with relevant information will be sent to mothers whose children are due for vaccination.

#### Incentive Offers

Conditional incentive offers will be specific to each child’s vaccination schedule. In our prior work [7,8], we identified a set of incentives (eg, pharmacy vouchers and birth certificates) that are likely to be acceptable to mothers. The specific incentives, their value, conditionality, and the timing of disbursement will be determined in discussion with local key informants.

### Implementation Strategies

Relevant implementation strategies will be identified in collaboration with local key informants, and a detailed logic model will be developed to guide study activities.

### Intervention Activities

Figure 1 describes the sequence of intervention activities. Pregnant women, enrolled in their third trimester, will receive a home visit from a CHW before the birth of their child, be registered with the Chanjo Kwa Wakati digital health system, and receive an individualized knowledge intervention to screen and counsel for common knowledge gaps and concerns about routine childhood vaccinations. After the birth of the child, the mother will receive individualized SMS text message reminders for upcoming vaccinations, messages aimed at mitigating persistent vaccination knowledge gaps, service notifications (eg, related to stockouts or service nonavailability), and conditional economic incentive offers aimed at encouraging timely vaccinations. CHWs will use the digital health system for work planning, recording vaccination dates and due dates, and following up on missed vaccination appointments and backstop the digital health system with phone calls and in-person visits as needed for vaccination reminders and assessing and addressing mothers’ knowledge gaps.

**Figure 1 figure1:**
[figure not shown]
Sequence of intervention activities. CHW: community health worker.

### Study Population

#### Sampling Area

The sampling area comprises 2 rural districts in Mwanza region and 2 rural districts in Shinyanga region, selected based on district-level information about vaccination rates, logistical considerations, and input from key informants.

#### Cluster Eligibility

Twenty clusters will be selected in each region for a total of 40 clusters. Clusters are defined as the catchment area of eligible health facilities in the sampling area. Eligible health facilities include public and public-designated (private not-for-profit facilities that serve the functions of public health facilities) hospitals, health centers, and dispensaries. Facilities must be operational, offer routine prenatal care and childhood vaccination services, have at least 2 active CHWs operating in the catchment area, and have reported at least 100 pregnancies or births in the year before study implementation. Eligibility will be determined initially using administrative data obtained from district offices and verified using surveys with health facilities.

#### Study Participants, Eligibility, and Recruitment

The study population will include 3 groups of participants.

##### Cross-Sectional Retrospective Cohort

This cohort (n=400) will be used for retrospective assessments of children’s vaccination records during their first year of life. Eligible participants will be mothers or legal guardians (henceforth referred to as *mothers*) of children aged 12 to 23 months, aged ≥15 years, and residing in the sampling area since the birth of the child.

Before recruiting this cohort, CHWs, with help from local key informants (eg, village leaders, health care providers, and traditional birth attendants), will compile a list of children aged 12 to 23 months residing in each cluster. The lists will be randomized, and mothers will be approached by the research team for eligibility determination, informed consent, and enrollment until 10 mother-child dyads from each cluster are enrolled into the study. Up to 40 additional women, who are not necessarily living in the study area but meet the other eligibility criteria, may be enrolled to pilot-test the study instruments.

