##### Longitudinal Prospective Cohort

This cohort (n=800) will be used for prospective assessments of children’s vaccination records during their first year of life. Eligible participants will be pregnant women in their last trimester of pregnancy, aged ≥15 years, residing in the sampling area, and expected to reside in the sampling area until the child reaches age 1 year.

Before recruiting this cohort, CHWs, with help from local key informants (eg, village leaders, health care providers, and traditional birth attendants) will compile a list of pregnant women residing in each cluster. The lists will be randomized, and pregnant women will be approached by the research team for eligibility determination, informed consent, and enrollment until 10 pregnant women from each cluster are enrolled into the study. One additional eligible woman will be enrolled from each cluster during each prospective enrollment round to account for loss to follow-up (refer to the *Retention* subsection).

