### Study Design

#### Cluster Randomized Trial Design

Forty rural health facilities and their catchment areas (*clusters*), 20 per region, will be randomized to an (A) early or (B) delayed onset study arm (Figure 2). From each cluster, 3 cohorts of 10 mother-child dyads (1 retrospective cohort and 2 prospective cohorts) will be enrolled into the study. For the retrospective cohort, 400 mothers of children aged 12 to 23 months (10/cluster) will be enrolled as a cross-sectional sample for retrospective assessments of children’s vaccination records during the first year of life. These cohorts, denoted by A1 and B1, will be part of the care-as-usual control group. For the longitudinal prospective cohort, 800 pregnant women in their last trimester of pregnancy will be enrolled during 2 rounds of enrollment (10 women/enrollment round/cluster) for prospective assessments of their children’s vaccination records during the first year of life. These cohorts are denoted by A2, A3, B2, and B3. In the first round of enrollment, 200 (50%) of the 400 prospective participants (those enrolled from early onset clusters; A2) will receive the intervention, and the other 200 (50%) participants (B2) will be part of the care-as-usual control group. In the second round of enrollment, all 400 participants (A3 and B3) will receive the intervention. In total, vaccination uptake and timeliness will be observed for 1200 children (n=600, 50% intervention group children and n=600, 50% nonintervention group children) during their first year of life. The nonintervention group children represent the *care-as-usual* control group in the trial.

The trial design, which analytically resembles a difference-in-difference design, allows for an analysis of the effectiveness of the intervention even in the context of contemporaneous changes in the rate and timeliness of vaccinations at the national level (eg, through national vaccination campaigns or changes in the vaccination schedule).

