#### Enrollment Survey

All participants will complete an enrollment survey. The survey will last approximately 45 minutes and assess knowledge and attitudes, sociodemographic characteristics of participants and their households, access barriers, digital literacy, residual knowledge gaps, and other correlates of vaccine uptake and timeliness. The mother’s engagement in prenatal care will be assessed via self-report and scanned prenatal care cards. For retrospective participants, the enrollment survey will also assess vaccination uptake and timeliness (Table 3), whereas for prospective participants, extensive contact information will be collected (refer to the *Retention* subsection).

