### Data Analysis

#### Quantitative Analysis of Intervention Effectiveness

The primary outcome measure of interest will be a continuous measure of vaccination timeliness, expressed as the delay, in days, between the vaccination due date and the date on which the vaccination was received for the third dose of the pentavalent vaccine, Penta3, due at age 14 weeks (Table 1). The secondary and other outcome measures include the timeliness and coverage of all vaccine doses recommended by age 1 year. Owing to the randomization, a comparison of mean outcomes between participants in the intervention group and those in the nonintervention group yields an unbiased estimate of the effect of the intervention.

To control for variation in sociodemographic characteristics across participants, seasonal effects, and other potential correlates of vaccination timeliness, outcomes will also be analyzed in a multivariable regression framework using accelerated failure time models with the completed vaccination dose as the failure event, age in days describing time to failure, and membership in the intervention versus control groups as the primary covariate of interest.

Robust SEs will be estimated to account for the clustering of observations across mother-child dyads enrolled from the same geographic clusters at the same time.

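### The pooled comparison mixes two sampling frames (child lists for 400 of 600 controls, pregnancy lists for everyone else), so randomization does not make it unbiased; the bias is of unknown size and uncertain sign

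*Protocol article*

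**What the plan says.** All references are to the protocol article.

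- **Frames.** Under Cross-Sectional Retrospective Cohort, community health workers with local informants "will compile a list of children aged 12 to 23 months residing in each cluster". Under Longitudinal Prospective Cohort, the same kinds of people "will compile a list of pregnant women residing in each cluster".
- **Allocation of cohorts to groups.** Cluster Randomized Trial Design says of the retrospective children: "These cohorts, denoted by A1 and B1, will be part of the care-as-usual control group". In the first prospective round A2 receives the intervention and "the other 200 (50%) participants (B2) will be part of the care-as-usual control group". Then: "In the second round of enrollment, all 400 participants (A3 and B3) will receive the intervention". The total is given as "n=600, 50% intervention group children and n=600, 50% nonintervention group children) during their first year of life".
- **What is randomized.** Cluster Randomization allocates clusters to early or delayed onset, and nothing else.
- **Estimate.** Quantitative Analysis of Intervention Effectiveness states that, because of the randomization, "a comparison of mean outcomes between participants in the intervention group and those in the nonintervention group yields an unbiased estimate". The regression that follows adjusts for sociodemographics, season and other correlates. It names no cohort or phase term.
- **Design description.** Cluster Randomized Trial Design likens the trial to a difference-in-difference design, but the analysis section does not specify that estimator.
- **Prenatal care.** Enrollment Survey says that the mother's "engagement in prenatal care will be assessed via self-report and scanned prenatal care cards", and this covers all participants.

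**The concern.** The two lists do not cover the same population. A mother who does not disclose her pregnancy, has no contact with the informants, or delivers before the list is drawn up is missed by the pregnancy list. Her child can still be on the child list a year later. Such a child can therefore be in A1 or B1, but not in B2 or in any intervention cohort.

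If these children tend to receive Penta3 later, the pooled control mean is raised with no intervention effect at all. The pooled contrast would then credit the intervention with part of a difference in sampling. This is separate from calendar time, residence rules and card availability, which also differ between the cohorts. Randomization gives no protection, because retrospective versus prospective membership was not randomized.

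**Working it through.** **1. Composition of the groups.** Controls: A1 + B1 = 400 and B2 = 200, total 600. Intervention: A2 = 200 and A3 + B3 = 400, total 600. Share from the child list: controls 400/600 = 66.7%; intervention 0/600.

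**2. The plan's own power, to see which contrast it describes.** Inputs from Statistical Power: SD 28 days, difference 7 days, 600 per group, cells of 10. Two-sided alpha 0.05 is assumed, because none is stated. Design effect DE = 1 + 9 × ICC; SE = 28 × √(2 × DE/600).

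| ICC | DE | SE (days) | Power | Stated |
|---|---|---|---|---|
| 0.05 | 1.45 | 1.95 | 0.949 | 0.95 |
| 0.10 | 1.90 | 2.23 | 0.881 | 0.88 |

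The stated figures are reproduced, so the power is that of the pooled 600 v 600 contrast.

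**3. Bias from the frame difference.** Let m be the mean delay among children of listed pregnancies under usual care. With u and D as the share and excess delay of children from unlisted pregnancies:

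- A1/B1 mean = (1 − u) × m + u × (m + D) = m + u × D
- Pooled control mean = (2/3)(m + u × D) + (1/3)m = m + (2/3) × u × D
- Intervention mean under no effect = m

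Bias = (2/3) × u × D. Neither u nor D is in the protocol; the values below are assumptions that show the range (days, positive = favours the intervention).

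| u | D = −15 | D = 0 | D = 15 | D = 30 | D = 45 |
|---|---|---|---|---|---|
| 5% | −0.5 | 0 | 0.5 | 1.0 | 1.5 |
| 10% | −1.0 | 0 | 1.0 | 2.0 | 3.0 |
| 15% | −1.5 | 0 | 1.5 | 3.0 | 4.5 |

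The case u = 10%, D = 30 gives 2.0 days, and 2.0/7 = 29% of the target difference. At ICC 0.05, the chance of a significant apparent benefit under no effect rises from 0.025 to 1 − Φ(1.96 − 2.0/1.95) ≈ 0.18. An opposing shift of u × D = 3.0 days in the A1/B1 mean would cancel this bias.

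**4. Contrasts free of the frame difference.** A2 v B2 compares pregnancy-list children with pregnancy-list children. In (A2 − A1) − (B2 − B1), a frame effect common to both arms cancels. The power for 7 days below treats cluster-by-phase cells as independent, as Statistical Power does.

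| Contrast | SE formula | Power, ICC 0.05 | Power, ICC 0.10 |
|---|---|---|---|
| A2 v B2 | 28 × √(2 × DE/200) | 0.55 | 0.44 |
| All cohorts, cluster and cohort effects | 28 × √(1.5 × 2 × DE/200) | 0.40 | 0.32 |
| (A2 − A1) − (B2 − B1) | 28 × √(4 × DE/200) | 0.31 | 0.25 |

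The first cohort is all control and the third all intervention. A model with a cohort term but no cluster effects therefore draws its estimate from A2 v B2 alone. If cells of the same cluster are positively correlated across phases, the last two rows are too low.

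**The case against.** The tempting stronger reading is that the pooled effect *is* biased towards benefit. The protocol does not support that.

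- It gives neither listing completeness nor Penta3 timing for unlisted pregnancies. Later vaccination in that group is plausible, not shown. Delivery before listing may be mere timing and need not mean poor contact with services.
- Both lists are compiled by community health workers with the same kinds of informants, including village leaders. Families unknown to them may be missing from both lists, which makes u smaller.
- Other selection in A1/B1 may run the opposite way. These children must have lived in the area since birth, whereas prospective women need only expect to stay. Under Missing Data (Study Limitations and Adaptations), if more than 10% of the retrospective sample lack cards and facility records do not help, enrollment continues until 400 have ascertainable outcomes. That could favour better-documented controls.
- The mean delay needs a date of receipt. A child who never received Penta3 has none, so part of the least-reached group may drop out of that mean.

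All of this stands, and it removes any firm claim on sign or net size. It does not rescue the statement that the pooled comparison is unbiased.

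It can also be said that the plan already handles the matter: prenatal care is collected, the regression admits other correlates, and the exact covariates may be in an analysis plan that is not shown. This stands in part, and one cannot conclude that prenatal care will go unused. But the sentence about the simple comparison of means is in the protocol, is wrong as written, and the power calculation rests on the same pooled contrast.

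Finally, the obvious remedy of restricting only A1/B1 to mothers with prenatal or health-worker contact would be asymmetric. Women listed through village leaders without such contact would stay in the prospective cohorts but be dropped from the retrospective controls.

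**Conclusion.** The point holds in this form. Two thirds of controls and no intervention children come from a post-birth child list, so the pooled contrast mixes a non-randomized difference in sampling frame with the intervention effect. The claim that randomization makes it unbiased is wrong. The bias from this source is (2/3) × u × D: 0.5 to 4.5 days towards benefit if u is 5% to 15% and D is 15 to 45 days, zero if D = 0, reversed if D is negative. These inputs are assumptions, and the formula takes the cohorts as otherwise comparable. Favouring the intervention is the more likely direction, but it is an inference. Nor should a reader infer that the design cannot give a sound estimate: A2 v B2 and a true difference-in-difference are free of this frame effect, at a clear cost in power.

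**What to change.** 1. In Quantitative Analysis of Intervention Effectiveness, withdraw the unbiasedness statement for the pooled contrast. Include a cohort or phase term, or specify the difference-in-difference estimator that the design section describes. In Statistical Power, restate the power for the contrast chosen.
2. Before A1/B1 enrollment, add one question to the enrollment survey of all cohorts: was the pregnancy known before birth to any of the informants who compile the pregnancy list, village leaders included? Outcomes Assessments ends retrospective participation after that survey, so the answer may not be recoverable later.
3. Tabulate B1 against B2 and A1 against A2 on fixed maternal characteristics and on the prenatal care already recorded, as a direct check of the two frames.
4. Beside the unrestricted result, give a sensitivity analysis that applies the same contact or prenatal-care criterion to every cohort, or adjusts for it. Do not restrict the retrospective controls alone.

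**Cost.** One survey question and some analysis wording. Recall after 12 to 23 months is imperfect, and some legal guardians will be unable to answer. The sensitivity analysis loses some sample: about 400 × u = 20 to 60 retrospective children for u of 5% to 15%, plus any prospective women who fail the criterion. The main cost is a less favourable stated power: on the independence assumption above, between 0.31 and 0.55 at ICC 0.05, against the stated 0.95.
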